### Statistical analysis

To test if there is a difference between the intervention group and the waiting list conditions on the primary outcome measure at second assessment (T_1_), ANCOVA will be used with the score on the second assessment as the dependent variable, the baseline score on the dependent measure as covariate, and condition as fixed factor [36]. Analysis of the data will be based on intention to treat. Missing values will be replaced with multiple imputation with fully conditional specification with at least five imputations. When statistically significant differences are found, a sensitivity analysis will be performed on the basis of different assumptions about the values of missing data. For the secondary outcome measures, limitations of daily functioning and diabetes control, the same analyses will be used. To determine if the expected positive result of CBT will be sustained at follow-up, scores at follow-up (T_3_) of patients treated with CBT directly or after the waiting period will be compared with the scores at post-treatment (T_1_ or T_2_) using paired *t*-tests.

Finally, we will test with multiple mediation which changes in the proposed fatigue maintaining cognitions and behaviours mediate the expected effect of the intervention on the primary outcome parameter of fatigue severity. The proposed mediators are factors that are thought to maintain fatigue severity. The mediation analysis will be conducted according to the approach of Preacher and Hayes [38]. Significance of the mediation effects will be determined using a non-parametric bootstrap approach which increases the power to detect significant effects even in small, non-normally distributed samples [38].

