### Sample size

Sample size calculation was based on the guidelines of Borm and colleagues (2007) [35] and Van Breukelen (2006) [36] for analysis of covariance (ANCOVA) in randomised controlled trials. On the primary outcome parameter, the CIS fatigue severity, we assumed a clinically relevant difference in post-treatment scores of 6 between the Dia-Fit and the waiting list condition [37]. With a power of 0.90, a two-sided alpha of 0.05 and a standard deviation of 8.6, a minimum number of 45 patients would be needed per condition when using a *t*-test. According to Borm and colleagues (2007) this number of patients can be multiplied by a ‘design factor’ when ANCOVA is used. This factor is one minus the squared correlation coefficient between baseline and second assessment of fatigue severity. As we have no data on which to base this correction, we used a conservative estimate of 1 as a factor which corresponds to a relatively low correlation between baseline and second assessment of about r = .20 (1 - .20^2^ = .96 ≈ 1). Assuming a drop-out rate of 25 %, 60 patients per condition need to be randomised (n = 120 in total).

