### Randomisation

Patients will be randomised in an equal ratio (1:1) to one of the two groups: 1) intervention group or 2) waiting list group. A computer randomisation program that is created by an independent statistical expert will be used for randomisation. Block randomisation is used with blocks of 6. Patients will be stratified into two groups: 1) patients recruited from hospitals and 2) patients recruited via media. A test assistant who is not involved in the study will do the random allocation in the presence of the patient after the baseline assessment. The researcher (JM) will also be present to plan appointments with the therapist and for the second assessment. The researcher is not blinded for treatment allocation. A researcher blinded for treatment allocation will do the statistical analysis.

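### The stated ANCOVA omits the recruitment-source stratum used in the randomisation; if source is prognostic beyond baseline, the test is slightly conservative (minor)

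*Protocol article*

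**What the plan says.** The Randomisation section sets 1:1 allocation and states: "Block randomisation is used with blocks of 6". It adds: "Patients will be stratified into two groups: 1) patients recruited from hospitals and 2) patients recruited via media".

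The Statistical analysis section names the primary model term by term. The dependent variable is the fatigue score at T1, and the right-hand side is "the baseline score on the dependent measure as covariate, and condition as fixed factor". The secondary outcomes (limitations in daily functioning and diabetes control) get the same analysis. No section says that recruitment source enters a model. Missing values are to be multiply imputed by fully conditional specification, and the article does not list the imputation variables.

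The Sample size section gives the planning figures: "we assumed a clinically relevant difference in post-treatment scores of 6 between the Dia-Fit and the waiting list condition", and "With a power of 0.90, a two-sided alpha of 0.05 and a standard deviation of 8.6, a minimum number of 45 patients" per condition for a t-test. On the ANCOVA correction it says: "we used a conservative estimate of 1 as a factor which corresponds to a relatively low correlation", about 0.20 between baseline and T1.

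**The concern.** Blocking within strata keeps the arms nearly balanced on recruitment source, so differences between the two sources contribute little to the true sampling variance of the treatment difference. A model without the stratum leaves those differences in the residual and therefore in the reported standard error. Where source is prognostic, the confidence interval is then somewhat too wide and the test runs below its nominal 5 %.

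Source could plausibly be prognostic. It is the only stratification factor, and the routes of entry differ: clinic patients are screened and invited by their own consultant, while media patients refer themselves. At stake is a little precision in the primary and secondary comparisons, and agreement between the analysis and the randomisation.

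**Working it through.** **Inputs from the article (Sample size, Randomisation).** Difference 6; SD 8.6; two-sided alpha 0.05; power 0.90; 45 per arm analysed; 25 % drop-out; 60 per arm randomised; baseline–T1 correlation r of about 0.20; blocks of 6; two strata.

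**Input assumed.** The partial R² of recruitment source for the T1 score, given baseline. The article gives no value. The range used is 0 to 0.10, with 0.20 as an extreme.

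**1. The plan's own figure.** With SD 8.6 and a difference of 6, noncentral-t power is 0.899 at 44 per arm and 0.905 at 45, so 45 reproduces. Then 45 / 0.75 = 60 per arm, 120 in total.

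**2. Standard error and power from the model formula.** The residual SD without the stratum is 8.6 × √(1 − 0.20²) = 8.6 × √0.96 = 8.426. The standard error is 8.426 × √(2/45) = 1.776. With the stratum it is multiplied by √(1 − R²). In points, an R² corresponds to a gap between equal-sized sources of 2 × 8.426 × √R².

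| Partial R² | Gap (points) | SE without | SE with | Power without | Power with |
|---|---|---|---|---|---|
| 0 | 0 | 1.776 | 1.776 | 0.916 | 0.916 |
| 0.02 | 2.4 | 1.776 | 1.759 | 0.916 | 0.921 |
| 0.05 | 3.8 | 1.776 | 1.731 | 0.916 | 0.929 |
| 0.10 | 5.3 | 1.776 | 1.685 | 0.916 | 0.941 |
| 0.20 (extreme) | 7.5 | 1.776 | 1.589 | 0.916 | 0.962 |

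The largest gain within the assumed range is 0.941 − 0.916 = 0.025.

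**3. Simulation of the actual design.** The table's power without the stratum ignores the fact that stratified blocking has already reduced the true variance. A simulation takes this into account: blocks of 6 within strata, N = 120, 25 % random drop-out, r = 0.20, equal strata, completers analysed without imputation, 8,000 runs per setting.

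| Partial R² | Type I error without | Type I error with | Power without | Power with |
|---|---|---|---|---|
| 0 | 0.048 | 0.049 | 0.913 | 0.912 |
| 0.02 | 0.051 | 0.054 | 0.908 | 0.910 |
| 0.05 | 0.049 | 0.054 | 0.914 | 0.923 |
| 0.10 | 0.042 | 0.052 | 0.920 | 0.938 |

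Monte Carlo error for the type I rates is √(0.05 × 0.95 / 8000) = 0.0024, so only the 0.042 lies clearly away from 0.05. At R² = 0.10 the mean model standard error without the stratum was 1.785 against an empirical 1.738, and 1.785 / 1.738 = 1.027, about 3 % too large. With the stratum the two were 1.695 and 1.713. The simulated power gain at R² = 0.10 is 0.938 − 0.920 = 0.018, somewhat below the 0.025 from the formula. A 20/80 split of sources gave similar results.

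**4. Why the conservatism is mild.** With exact balance within strata among completers, the type I error without the stratum would be 2 × [1 − Φ(1.96 / √(1 − R²))]. At R² = 0.10 that is 2 × [1 − Φ(2.066)] = 0.039. Drop-out disturbs the balance and moves the rate back towards 0.05, hence the simulated 0.042.

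**The case against.** The strongest counter-argument is that nothing in the article shows recruitment source to be prognostic. The Randomisation section gives no prognostic reason for stratifying. The Sample size section says the authors have no data even for the baseline–T1 correlation. Both sources meet the same fatigue entry criteria, and any part of a source difference that baseline explains is already removed by the covariate. A T1 gap of 5 to 6 points between sources would be about as large as the treatment difference the trial is powered for. This stands: the loss is conditional, and its range has to start at zero.

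Four stronger readings are tempting, and the documents support none of them.

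- **The standard error is wrong and power is lost in any case.** At R² = 0 the standard error is correct, and simulated power is 0.913 without and 0.912 with the stratum, so adjustment does not always help.
- **The trial is underpowered or its type I error is inflated.** The omission can only make the test conservative. The sample size uses a design factor of 1 and so takes no credit for covariates; power without the term stayed above 0.90 in every setting.
- **Media patients may respond differently to treatment.** That is a treatment-by-source interaction, which a main-effect term does not address.
- **The imputation model is mis-specified.** The article lists no imputation variables, so no fault can be shown there.

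It may also be said that a separate analysis plan, not shown, could already include the stratum. That does not remove the point, because the article names the model terms one by one and the stratum is not among them.

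**Conclusion.** The point holds in a limited, conditional form. Randomisation is stratified by recruitment source, and the stated ANCOVA for the primary and secondary outcomes leaves it out. If source predicts the T1 score beyond baseline, the reported standard error is slightly too large and the test slightly conservative; otherwise nothing is lost.

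Over the assumed partial R² of 0 to 0.10, type I error without the stratum runs from about 5 % down to about 4.2 %. The power gain from including it is about 0 to 2.5 points by formula and at most about 1.8 points in the simulation. These sizes rest on the article's SD, difference and r, on 45 completers per arm, and on drop-out unrelated to source or outcome. There is no bias, and the planned 90 % power and the sample size are unaffected. This is a minor efficiency improvement.

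**What to change.** In the Statistical analysis section, prespecify recruitment source (hospital/media) as a fixed factor alongside baseline score and condition in the ANCOVA for the primary and secondary outcomes. When the imputation model is written down, keep it consistent with that analysis model by including the same factor.

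The cost is one sentence and one degree of freedom. The variable is already recorded for the randomisation, and the sample size does not change. The Trial status section describes recruitment as ongoing, so the term can be fixed before outcome data are examined; added later, it could look post hoc.

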### Assessments

The baseline assessment (T_0_) consists of two appointments at the ECCF. During both test sessions patients will complete questionnaires (Table 2). In the two weeks between the two sessions patients will wear an actometer to measure physical activity [27]. Patients will also record their symptoms and activities in a diary. In addition, blood glucose variability and HbA_1c_ will be assessed. After the baseline assessment patients will be randomised to either the Dia-Fit intervention group or the waiting list group. After five months the second assessment will be done (T_1_), consisting of the same measures as at baseline assessment. After T_1_ the waiting list group will start with Dia-Fit. The waiting list group will receive an extra assessment after therapy (T_2_). All patients will be assessed six months after finishing Dia-Fit (T_3_). T_2_ and T_3_ will consist of a limited number of measures (Table 2).

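### The test of whether benefit is sustained compares T3 only with post-treatment, so unchanged scores in patients who never improved would count as sustained

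*Protocol article*

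**What the plan says.** The Statistical analysis section of the protocol article sets one randomised efficacy test: "ANCOVA will be used with the score on the second assessment as the dependent variable", with the baseline score as covariate and condition as fixed factor. The secondary outcomes are handled in the same way.

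The Assessments section gives the order of events for the control arm: "After T_1_ the waiting list group will start with Dia-Fit", and then "The waiting list group will receive an extra assessment after therapy". That extra assessment is T2. All patients are assessed at T3, six months after finishing treatment.

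The follow-up analysis has a stated purpose, "To determine if the expected positive result of CBT will be sustained at follow-up", and a stated method: T3 scores "of patients treated with CBT directly or after the waiting period will be compared with the scores at post-treatment", the reference being "T_1_ or T_2_) using paired *t*-tests". The Statistical analysis section names T2 nowhere else. The end of the Background section lists the long-term effect of Dia-Fit among the things the trial will investigate.

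**The concern.** A claim that a result is sustained needs two parts: there was a gain, and the gain is still there at T3. The stated test addresses only change after the end of treatment. For the Dia-Fit arm the first part comes from the randomised comparison at T1. For the waiting list no stated efficacy analysis measures the gain over its own treatment. In neither arm is T3 set against a pre-treatment score.

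A waiting-list patient who did not improve between T1 and T2 and stays flat to T3 contributes a change of about zero, which counts towards a sustained effect. With 1:1 allocation, such patients come from an arm that makes up about half of the follow-up sample.

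A second risk arises only if the arms are combined. If the waiting list gained less and so had less to lose, its flat scores dilute a real loss in the Dia-Fit arm. The favourable outcome of this test is a non-significant one, so lost power works in favour of the claim.

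**Working it through.** **Plan's own figure.** The Sample size section gives a difference of 6 points, SD 8.6, two-sided alpha 0.05 and power 0.90. The t-test solution is 44.16, so 45 per arm. Allowing for 25 % drop-out, 45 / 0.75 = 60 per arm. The stated numbers reproduce. They concern T1 and are not in dispute.

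**What each stated comparison tells us, by arm.**

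| Question | Dia-Fit arm | Waiting list |
|---|---|---|
| Gain over own treatment | Between-arm ANCOVA at T1 | No stated efficacy analysis (would be T1 to T2) |
| Change after treatment | T3 against T1 | T3 against T2 |
| T3 against pre-treatment | Not stated (T0) | Not stated (T1) |

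The second row alone cannot separate a gain that was kept from a gain that never occurred. This holds whether the paired tests are run by arm or combined.

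**Size of the masking risk if the arms are combined.** The article gives no SD for the T3 minus post-treatment change, so 7 to 10 is an assumption. The other inputs are 45 evaluable patients per arm (Sample size section), two-sided alpha 0.05, and a loss of 3 points in the Dia-Fit arm (half of the 6-point difference; an assumption).

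Power is from the noncentral t with n − 1 degrees of freedom and noncentrality mean / (SD / √n).

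- *Dia-Fit arm alone:* mean 3, n = 45. At SD 8.6 the noncentrality is 3 / (8.6 / √45) = 2.34.
- *Pooled, waiting list with no gain and no change:* mean (3 + 0) / 2 = 1.5, n = 90, SD √(SD² + 1.5²). At SD 8.6 this is √(73.96 + 2.25) = 8.73, and the noncentrality is 1.5 / (8.73 / √90) = 1.63.
- *Pooled, both arms lose 3:* mean 3, n = 90. At SD 8.6 the noncentrality is 3 / (8.6 / √90) = 3.31.

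| SD of change | Dia-Fit arm alone | Pooled, waiting list flat | Pooled, both lose 3 |
|---|---|---|---|
| 7 | 0.80 | 0.50 | 0.98 |
| 8 | 0.69 | 0.41 | 0.94 |
| 8.6 | 0.63 | 0.36 | 0.91 |
| 10 | 0.50 | 0.29 | 0.80 |

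**Sensitivity to the SD.** Taking the protocol's SD of 8.6 at both times and its low correlation of about 0.20, the SD of change is 8.6 × √(2 × 0.8) = 10.9, just outside the range above. The three powers are then 0.44, 0.25 and 0.74. The ordering does not change.

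**Can the waiting list's gain be measured?** With 45 patients, a paired T1-to-T2 comparison has power of about 0.98 or more for a 6-point change over SD 7 to 10, and 0.95 at SD 10.9.

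**The case against.** Five arguments stand against the point.

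1. *Pooling is not stated.* The plural in the reference to paired t-tests fits one test per arm or per outcome as well as a combined test. This stands: a reader might infer that the plan pools the arms, but the text does not settle it. The power illustration applies only if it does. The missing gain and the missing pre-treatment anchor do not depend on it.

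2. *T2 may have another use.* The Treatment adherence section correlates adherence ratings with the pre- to post-treatment change in the primary outcome and is not limited to one arm. For waiting-list patients that change would need T2. So one cannot say that T2 serves solely as the reference for T3. The correlation does not, however, measure the gain.

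3. *A T1-to-T2 change cannot show that Dia-Fit worked in the waiting list.* Correct. It has no concurrent control. A reader might also infer that the plan leaves efficacy unproven for half the patients. The documents do not support that: efficacy rests on the randomised comparison at T1, and the waiting list is a randomised sample of the same population receiving the same intervention. What the T1-to-T2 change supplies is a description of the gain that is said to be sustained.

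4. *The zero-gain waiting list is an extreme case.* It is, and nothing in the article makes it likely. If both arms gain and lose alike, combining them is the better choice.

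5. *By-arm and within-arm summaries may be in a full protocol or analysis plan.* They may. But the article does more than leave detail out: it fixes the aim, the reference point and the test, and that test does not by itself answer the aim.

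**Conclusion.** The point holds in a limited form. As written, the judgement that benefit is sustained rests on change after treatment alone. No stated efficacy analysis measures the waiting list's gain, and neither arm's T3 score is tied back to pre-treatment. Lack of change in patients who did not improve would support the claim.

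Masking of a loss in the Dia-Fit arm is conditional on combined arms and a smaller gain in the waiting list. At the extreme, with 45 per arm and an assumed SD of change of 7 to 10, power for a 3-point loss falls from 0.50–0.80 to 0.29–0.50; with equal gains and losses, combining raises it to 0.80–0.98. The plan as stated does not check which case applies.

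The primary and secondary comparisons at T1 are untouched. This is a minor-to-moderate point about the long-term claim.

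**What to change.** Amend the follow-up paragraph of the Statistical analysis section:

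- State whether the T3 versus post-treatment comparison combines the arms. Keep the combined estimate, and give it by arm as well, with 95 % confidence intervals.
- Report beside it T3 minus pre-treatment (T0 for the Dia-Fit arm, T1 for the waiting list) and the waiting list's T1-to-T2 change. Label these as uncontrolled within-arm changes.
- Claim a sustained effect only where a gain was seen and is still present at T3.

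Table 2 shows CIS fatigue, SIP8, HbA1c and glucose variability at T0 to T3, so no new data are needed. The cost is a little more analysis and wider by-arm intervals: at SD 8.6 the 95 % half-width is about 2.6 points with 45 patients (2.015 × 8.6 / √45) against about 1.8 with 90 (1.987 × 8.6 / √90).

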## Discussion

To our knowledge, this study is the first randomised controlled trial testing the efficacy of a web-based cognitive behavioural intervention for chronic fatigue in patients with T1DM. Chronic fatigue is highly prevalent in T1DM and is experienced by patients as one of the most disabling symptoms of the illness. An effective treatment focusing on fatigue in patients with T1D is not yet available.

The blended-care character of Dia-Fit, consisting of web-based information, assignments and e-mail contact supported by face-to-face sessions, is a promising approach for both patients and therapists. The tailored approach of Dia-Fit makes it possible to concentrate on fatigue maintaining factors that are relevant for each individual patient.

In conclusion, the results of the described study will provide information about the efficacy of CBT for severe fatigue in patients with T1DM and, one hopes, will contribute to the treatment of fatigue in T1DM.

## Trial status

Recruitment of the Dia-Fit study is ongoing. The recruitment started in January 2014 and is expected to end in February 2016.

## Abbreviations

AE: adverse event
ANCOVA: analysis of covariance
CBT: cognitive behaviour therapy
CIS: Checklist Individual Strength
ECCF: Expert Center for Chronic Fatigue
HbA_1c_: haemoglobin A_1c_
RCT: randomised controlled trial
SAE: serious adverse event
SIP: Sickness Impact Profile
T1DM: type 1 diabetes mellitus
